## Abstract

**Background:**

Postpoliomyelitis Syndrome (PPS) is a complex of late onset neuromuscular symptoms with new or increased muscle weakness and muscle fatigability as key symptoms. Main clinical complaints are severe fatigue, deterioration in functional abilities and health related quality of life. Rehabilitation management is the mainstay of treatment. Two different therapeutic interventions may be prescribed (1) exercise therapy or (2) cognitive behavioural therapy (CBT). However, the evidence on the effectiveness of both interventions is limited. The primary aim of the FACTS-2-PPS trial is to study the efficacy of exercise therapy and CBT for reducing fatigue and improving activities and quality of life in patients with PPS. Additionally, the working mechanisms, patients' and therapists' expectations of and experiences with both interventions and cost-effectiveness will be evaluated.

**Methods/Design:**

A multi-centre, single-blinded, randomized controlled trial will be conducted. A sample of 81 severely fatigued patients with PPS will be recruited from 3 different university hospitals and their affiliate rehabilitation centres. Patients will be randomized to one of three groups i.e. (1) exercise therapy + usual care, (2) CBT + usual care, (3) usual care. At baseline, immediately post-intervention and at 3- and 6-months follow-up, fatigue, activities, quality of life and secondary outcomes will be assessed. Costs will be based on a cost questionnaire, and statistical analyses on GEE (generalized estimated equations). Analysis will also consider mechanisms of change during therapy. A responsive evaluation will be conducted to monitor the implementation process and to investigate the perspectives of patients and therapists on both interventions.

**Discussion:**

A major strength of the FACTS-2-PPS study is the use of a mixed methods design in which a responsive and economic evaluation runs parallel to the trial. The results of this study will generate new evidence for the rehabilitation treatment of persons with PPS.

**Trial registration:**

Dutch Trial Register NTR1371.

## Background

Poliomyelitis anterior acuta is an acute viral disease that attacks the anterior horn cells of the spinal cord and the motor neurons of the lower brain stem resulting in flaccid paresis or paralysis. Usually there is partial and sometimes complete recovery from the self-terminating disease. However, many people with a history of poliomyelitis report late onset neuromuscular symptoms and a decline in functional abilities. These late symptoms are referred to as Postpoliomyelitis Syndrome (PPS) and include new or increased muscle weakness, abnormal muscle fatigability, generalized fatigue, muscle atrophy, muscle and joint pain, muscle cramps and cold intolerance [1].

The prevalence of PPS has been reported from 15% to 80% of all patients with previous paralytic polio depending on the criteria applied and population studied [2]. Nearly 60% of a sample of Dutch survivors of the 1956 polio outbreak experience late onset polio sequelae [3]. In Western countries, where the large epidemics date back to the 1940s and 1950s, many polio survivors are now experiencing progressive complaints related to PPS. The World Health Organization (WHO) estimates that 10 to 20 million polio survivors are alive worldwide, and some estimates suggest that 4 to 8 million of them may develop PPS [4]. Although, the efforts of the Global Polio Eradication Initiative of the WHO initiated in 1988, led to an enormous reduction in the number of acute polio cases globally ever since, polio is still a relevant problem. In Western Africa and in South Asia polio is still endemic and spread of the virus from these countries causes new outbreaks in countries that were certified as polio free. Therefore, new cases of PPS can be anticipated in the coming decades.

Fatigue is one of the most frequent complaints of PPS [5-7] and it is typically described as tiredness or lack of energy that increases with physical activity and decreases with rest [8]. In a study on disability and health problems in 76 Dutch patients with PPS, 78% of the subjects selected fatigue as their major problem [9]. Subjects with PPS experience higher levels of fatigue than healthy controls [10,11]. Fatigue has a negative impact on activities of daily living and there is evidence that post-polio related fatigue is an important factor for the reduced health related quality of life (HRQoL) in polio survivors [12].

In current practice, rehabilitation management is the mainstay of treatment for PPS. Rehabilitation aims to improve patients' capacities to perform activities of daily living and adapt performance (i.e. actual behaviour) to the available capacities. We expect that a reduction of the imbalance between patients' capacities and performance will lead to a reduction in fatigue and improvement in activities and HRQoL. There are two possible approaches to achieve this goal; exercise therapy and cognitive behavioural therapy (CBT). However, evidence to support the effectiveness of either approach is still limited.

The insufficient evidence to support exercise consists of contradictory and incomplete information in the literature. On the one hand, PPS patients are advised to avoid muscular overuse and intensive training as this could worsen symptoms such as muscle weakness and fatigue and provoke a further loss of muscular strength [1]. On the other hand, physically active PPS patients were found to have less symptoms of fatigue than sedentary patients [13]. It is unclear whether symptoms of fatigue are cause or result of physical inactivity. A systematic review on exercise therapy for neuromuscular diseases included ten studies on muscle strengthening exercises and aerobic exercises in PPS of which five demonstrated significant positive effects on muscular strength and aerobic capacity without generating any adverse effects. However, all these studies had to be qualified as having insufficient or limited methodological quality [14]. This led to the conclusion that there is insufficient evidence for the effectiveness of exercise for patients with PPS and that future, preferably multi-centre, studies are needed. A recent study on the short-term effectiveness of home- and hospital- based aerobic exercise showed improvement on fatigue and quality of life [15]. However results were not compared with a control group and long-term effectiveness was not evaluated in this study.

There is broad evidence for the effectiveness of CBT in reducing fatigue in chronic fatigue syndrome, fatigued post cancer survivors and multiple sclerosis [16-19]. However, there are no studies of CBT for fatigue in PPS.

The evidence for a cognitive behavioural approach in PPS is currently limited to results from an uncontrolled pilot study in which cognitive behavioural strategies are incorporated in a comprehensive multidisciplinary rehabilitation program [20]. Although significant reductions in fatigue symptoms were found, it is unclear whether these effects can be ascribed to the cognitive behavioural components of the intervention.

We anticipate that exercise therapy and CBT are both effective in reducing fatigue and improving activities and HRQoL in patients with PPS compared to the usual care. The FACTS-2-PPS study aims to give insight in the efficacy of both interventions for patients with PPS. As secondary outcomes, the working mechanisms, patients' and therapists' expectations of and experiences with both interventions and cost-effectiveness will be evaluated. These aims have led to the following research questions:

(1) Does exercise therapy for patients with PPS reduce fatigue and improve activities and HRQoL as compared to usual care?

(2) Does CBT for patients with PPS reduce fatigue and improve activities and HRQoL as compared to usual care?

(3) What are the generic and disease-specific determinants for treatment success of exercise therapy and CBT?

(4) What are patients' expectations of and experiences with exercise therapy and CBT?

(5) What is the cost-effectiveness of exercise therapy and CBT compared to usual care?

## Methods/Design

### Study design

A multi-centre, single-blinded randomized controlled trial (RCT) with 6 months follow-up will be conducted to evaluate the efficacy of exercise therapy and CBT compared to usual care in patients with PPS (Figure 1). To gain insight into patients' expectations and experiences, a responsive evaluation will be conducted. To determine the cost-effectiveness, an economic evaluation will be conducted alongside this RCT. The study protocol was approved by the Medical Ethics Committee of the Academic Medical Centre (AMC) and all participating centres granted approval to participate.

**Figure 1 F1:**
[figure not shown]
**Study design**.

### Study population

All patients will be recruited from outpatient clinics of the AMC Amsterdam; the University Medical Centre Utrecht (UMCU); the University Medical Centre Nijmegen (UMCN) or the affiliate rehabilitation centres. Case histories are checked to screen for potentially eligible patients. Patients willing to give signed consent are evaluated by a physician to check in and exclusion criteria (Table 1). The sample size was calculated for this three-arm trial based on the comparison treatment (exercise therapy or CBT) versus usual care, with equal allocation across treatment arms and 4 repeated measurements (at entry (pre-treatment), at 4 months (post-treatment), at 3 months follow-up (short-term follow-up) and at 6 months follow-up (long-term follow-up), respectively), with an estimated correlation coefficient of the repeated measurements of rho = 0.79 (based on unpublished data from a reproducibility study in 37 PPS patients), a clinical relevant improvement of 8 points on the CIS-fatigue scale (for both treatments) [17] and an estimated standard deviation in each treatment group of 9.3. The total sample size needed to detect this difference on a 5% level of significance (two tailed) with a power of 90% was 24 subjects in each group [21]. We expect a drop-out rate of maximal 10%, based on a previous trial in this patient group [22]. Therefore 81 patients will be recruited.

**Table 1 T1:** In- and exclusion criteria

Inclusion criteria
(1) diagnosis of PPS according to the criteria of March of Dimes [1]

(2) severe perceived fatigue (CIS-fatigue > = 35) [47]

(3) age between 18 and 75 years

(4) life-expectancy longer than one year

(5) walking-ability at least indoors with or without a walking aid

(6) ability to cycle on a cycle ergometer against a load of at least 25 Watt

**Exclusion criteria**

(1) use of psychotropic drugs or other psychiatric treatment

(2) clinical depression (BDI-PC > 6) [48]

(3) disabling co-morbidity interfering with the intervention programs or influencing outcome parameters (including cardiopulmonary disease, epileptic seizures, poorly regulated diabetes mellitus)

(4) respiratory insufficiency (FVC < 50%pred or CO_2 _retention) or assisted ventilation

(5) cognitive impairment

(6) insufficient mastery of the Dutch language

(7) pregnancy

### Randomization and blinding

Patients will be assigned to the rehabilitation centre that is nearest to their home village. Randomization will be stratified per centre. Patients fulfilling both inclusion and exclusion criteria will be randomized to one of three groups: (1) exercise therapy + usual care, (2) CBT + usual care, or (3) usual care. The randomization scheme is computer-generated and will be done by creating random blocks of sequences with variable block sizes of 3 and 6. The investigator who will perform the randomization will inform the patient and, in case of allocation to exercise therapy or CBT also the therapist of the group allocation.

The investigators that are responsible for the inclusion will be blinded. Outcomes will be assessed by blinded and independent outcome assessors. At the beginning of the assessment patients will be instructed not to reveal their group allocation to the investigators. To evaluate the success of blinding, the investigator will be asked at each measurement, to guess the treatment assignment of the patient, with options 'CBT', 'exercise therapy', 'usual care only' and 'unknown'. Analyses will be performed blinded for treatment allocation.

### Interventions

#### Usual care

The patients in the control and intervention groups will all receive usual care. Usual care for PPS patients may include usage of assistive devices, orthoses, physical therapy, and medication. Patients will not be restricted in their activities. Co-interventions will be monitored throughout the study.

#### Exercise therapy

Exercise therapy is designed specifically to enhance physical capacity. The intervention has a duration of 16 weeks and consists of (1) a home-based aerobic training program three times weekly and a (2) supervised group training consisting of muscle strengthening and functional exercises once a week. The therapy will be supervised by specifically trained physiotherapists. An unblinded member of the project group will supervise the therapists and perform integrity checks on each treatment location.

(1) The home-based training program consists of individually tailored aerobic exercise on a cycle ergometer. Patients will be supplied with a cycle ergometer, a log book with training instructions and a training scheme at home. Heart rate will be continuously measured with a heart rate monitor. Furthermore, in the log book patients will document the number and duration of treatment sessions, the training load, perceived exertion on the Borg Rated Perceived Exertion Scale [23] and possible complaints after the training session. Training intensity will be gradually increased from 60% of the Heart Rate Reserve (HRR) to 70% HRR, in accordance with the American College of Sports Medicine guidelines for aerobic training in healthy adults [24] and persons with chronic diseases and disabilities [25]. The duration of the training sessions will gradually be increased from 20 to 30 minutes per session and sessions are divided into prescribed exercise bouts which are interspersed with short rest periods of unloaded cycling. The duration of exercise bouts will be gradually increased from 2 minutes at the start of the program to 13 minutes at the end of the program.

Warming-up and cooling-down consists of 5 minutes unloaded cycling. Feasibility of the training schemes is weekly checked by one of the therapists by reading out the heart rate monitors and checking the log books. When necessary, adjustments to the training schemes will be made.

(2) The supervised group training consists of individually tailored muscle strengthening exercises and functional exercises in 1-hour group sessions. Sessions will be divided into a 5-minute warm-up period of aerobic exercises, 30 minutes of muscle strengthening, 20 minutes functional exercises and a 5-minute cool-down period. Muscle strengthening exercise selection and dosage will be determined by the therapist at a separate visit to the treatment location before the start of the program. Muscle groups and accompanying exercises will be selected based on patients MRC-scores [26] and reported problems in daily activities. Exercises are selected based on the best expected effects on physical functioning.

Muscle groups with MRC scores less then 3 are not selected and quadriceps muscles are always selected when this muscle group has a MRC score of at least 3. Training load will be based on the 1-RM test [27]. In the first 4 weeks, training load will be 50% of 1-RM, each exercise consists of 3 sets with 2 minutes rest between a set and number of repetitions will be increased from 8 to 20 during 4 weeks. When the desired number of repetitions with the current load is reached, training load is increased in week 5 and 9 to 60 and 70% respectively, and the number of repetitions is increased in the same manner as prescribed for the first 4 weeks [28].

#### Cognitive behavioural therapy

CBT will be directed at frequently reported perpetuating factors of fatigue in slowly progressive neuromuscular disorders [29]. They may involve dysfunctional cognitions with respect to the disease itself, to pain and to fatigue [30], dysfunctional attention to pain or fatigue symptoms, deregulation of sleep [30,31], deregulation of physical, social and/or mental activities [30,31], and low social support and negative social interactions [32]. For each factor a standardized module is available as part of the intervention. Because of the variability of relevant perpetuating factors in PPS patients, therapy will be customized to each individual. To determine which modules will be necessary, each perpetuating factor will be measured with specific questionnaires (Table 2). The number of sessions will be determined by the number of modules used and will vary between 12 and 16 sessions, each with a duration of 1 hour during a 4 months period. Experienced cognitive behavioural therapists will treat the patients. The therapists will be trained in the protocol and the use of instruments to determine which module should be included in the therapy. Role-playing is an important part of this training. In the first CBT session individualized concrete behavioural goals of the therapy are formulated by the patient with help of the therapist. These goals are formulated in terms of concrete behaviours the patient wants to perform if he is not extremely fatigued anymore. Appendix 1 gives an overview of cognitive and behavioural techniques that can be used during CBT for each perpetuating factor of fatigue.

**Table 2 T2:** Instrumentation for module selection CBT

Perpetuating factor for fatigue	Instrumentation
1. Dysfunctional cognitions with respect to the disease	Impact of Event Scale [49] Pictorial Representation of Self and Illness Measure (PRISM) [50] Illness Cognitions Questionnaire (ICQ) [51]

2. Dysfunctional cognitions with respect to pain	Medical Outcome Study 36-Item Short-Form Health Survey (SF-36; domain: pain) [52] Daily Observed Pain (DOP) [53] Pain Catastrophizing Scale (PCS) [54]

3. Dysfunctional cognitions with respect to fatigue	Self-Efficacy Scale [18] Jacobsen Fatigue Catastrophizing Scale (J-FCS) [55]

4. Dysfunctional attention to fatigue and pain	Illness Management Questionnaire (IMQ) [56]

5. Deregulation of sleep	Sickness Impact Profile (SIP; domain: sleep and rest) [57] Symptom Checklist-90 (SCL-90; domain: sleep) [58]

6. Deregulation of physical activities	Chronic Fatigue Syndrome-activity questionnaire (CFS-AQ; domain: physical activity) [59]

7. Deregulation of social activities	Medical Outcome Study 36-Item Short-Form Health Survey (SF-36; domain: social functioning) [52] Chronic Fatigue Syndrome-activity questionnaire (CFS-AQ; domain social activity) [59] Sickness Impact Profile (SIP; domain: social interaction) [57]

8. Deregulation of mental activities	Checklist Individual Strength (CIS; domain: concentration) [47] Sickness Impact Profile (SIP; domain: alertness/intellectual functioning) [57] Chronic Fatigue Syndrome-activity questionnaire (CFS-AQ; domain: mental) [59]

9. Low social support and negative social interactions	Social Support Inventory-Interactions (SSL-I_08) [60] Social Support Inventory-Discrepancies (SSL-D_08) [60]

### Compliance and attrition

Compliance will be assessed by recording the number of treatment sessions (CBT or group exercise sessions) attended and, for the patients randomized to exercise therapy, also the total time spent to aerobic exercise on the bicycle ergometer at home will be recorded in a log book.

### Outcomes

#### Efficacy and working mechanisms

Outcome measures are presented in Table 3. Our primary outcome measure is fatigue. Additionally, daily activity performance and HRQoL will be evaluated. Secondary outcomes are categorised in accordance with the International Classification of Functioning (ICF) [33] on the level of body functions, activities and participation and personal factors. As potential effect modifiers the following parameters will be studied; demographic variables, main complaints of PPS, disease severity, co-morbidity, serum creatine kinase activity and the ICF environmental factors; social support, HRQoL of the partner, coping of the partner and caregiver burden. Two secondary outcome measures on the level of body functions; cardio-respiratory fitness and neuromuscular capacity will be described in greater detail.

**Table 3 T3:** Outcome measures and instrumentation

	Instrumentation	T1	T2	T3	T4

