**Primary outcome measures**					

Fatigue	Checklist Individual Strength (CIS; domain: fatigue) [47]	X	X	X	X

Daily activity performance	Sickness Impact Profile 68 (SIP-68; domains: mobility range, mobility control, social behaviour) [61]	X	X	X	X

HRQoL	Medical Outcome Study 36-Item Short-Form Health Survey (SF-36) [52]	X	X	X	X

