#### Economic evaluation

Cost-effectiveness and cost-utility will be evaluated from a societal perspective. The costs will include direct health care costs of visits to general practitioners, medical specialists, therapists, medications and assistive devices, direct non-health care costs i.e. non-reimbursable costs for complementary medicine and over-the-counter medication, and indirect, non-health care costs of changes in paid and unpaid work. All these data will be collected via cost diaries.

Resource use will be valued following the procedures outlined by the Dutch Manual of Costing [40]. Where standard cost prices are not available, tariffs or professional fees will be used to estimate costs. The costs of medications will be estimated using the prices reported by the Royal Dutch Society for Pharmacy. Productivity loss costs from paid work will be estimated using both the human capital approach and friction cost method. The productivity loss costs from unpaid work will be determined using a shadow price. Cost prices of the interventions will be determined by a bottom-up calculation.

The effect measures used in the economic evaluation will be our primary outcome measure fatigue and HRQoL measured with the EuroQol-5D [41] at the four different time measurements. Utilities will be derived using the Dutch tariffs and used to determine quality-adjusted life years (QALYs) [42,43].

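### The text names fatigue as the single primary outcome and the trial is sized on it alone, but Table 3 lists three primary outcome measures

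*Protocol article*

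**What the plan says.** Three places in the protocol article point to one primary outcome.

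- Outcomes, Efficacy and working mechanisms: "Our primary outcome measure is fatigue. Additionally, daily activity performance and HRQoL will be evaluated".
- Economic evaluation: "The effect measures used in the economic evaluation will be our primary outcome measure fatigue and HRQoL measured with the EuroQol-5D".
- Study population, where the sample size is derived, uses one scale only: "a clinical relevant improvement of 8 points on the CIS-fatigue scale (for both treatments", with SD 9.3, correlation 0.79 over four measurements, two-sided 5% and 90% power. This gives 24 per group, and 81 in total after 10% drop-out.

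Table 3 says otherwise. Under the heading "Primary outcome measures" it has three rows: CIS-fatigue, "Sickness Impact Profile 68 (SIP-68; domains: mobility range, mobility control, social behaviour") and "Medical Outcome Study 36-Item Short-Form Health Survey (SF-36"), the last with no score named. A separate heading for secondary outcomes follows, arranged by ICF level, and neither the SIP-68 nor the SF-36 row appears there.

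The aims name all three domains. The abstract gives the primary aim as "to study the efficacy of exercise therapy and CBT for reducing fatigue and improving activities and quality of life in patients with PPS". Research question 1 in the Background asks "Does exercise therapy for patients with PPS reduce fatigue and improve activities and HRQoL as compared to usual care", and question 2 asks the same of CBT. Statistical Analyses applies GEE to primary and secondary outcomes for both interventions against usual care and gives no order among them.

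**The concern.** A reader of the text and a reader of Table 3 would disagree on what the trial's main result is. The two measures in dispute have no clear status elsewhere. The Outcomes text introduces them as additional but does not call them secondary, and the abstract's list of assessments also sets activities and quality of life apart from the secondary outcomes. Table 3 is the only place that classifies them explicitly.

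Two things are at stake. First, if the three measures are all primary, the sample-size justification covers only one of them. Second, while the status is open, a result on the SIP-68 or SF-36 could be presented as a primary finding after the data are known, with no error control planned for that use. An analysis plan written from this protocol would inherit the ambiguity.

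**Working it through.** **1. The stated sample size.** Inputs from Study population: difference d = 8, SD s = 9.3, ρ = 0.79, T = 4 measurements including entry, two-sided α = 0.05, power 0.90.

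- Without the repeated-measures factor: n = 2s²(1.960 + 1.282)²/d² = 2 × 86.49 × 10.507/64 = 28.40.
- Compound-symmetry factor: (1 + 3 × 0.79)/4 = 0.8425.
- n = 28.40 × 0.8425 = 23.93, so 24 per group.
- Drop-out: 24/0.9 = 26.7, so 27 per group; 27 × 3 = 81.

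The plan's figures reproduce exactly. They use the full 5% for one CIS-fatigue comparison. No difference or SD is given for the SIP-68 or SF-36, so no power can be attributed to them.

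**2. Number of tests under each reading.**

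- Text: 1 outcome × 2 comparisons with usual care = 2 tests.
- Table 3: 3 outcomes × 2 comparisons = 6 tests, taking one score per instrument and one contrast over time.

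**3. Family-wise error at 5% per test, if any single positive counts.** With independent tests it is 1 − 0.95² = 9.75% for two tests and 1 − 0.95⁶ = 26.5% for six. The shared usual-care arm with equal allocation gives correlation 0.5 between the two comparisons. The correlation between outcomes is not in the document and is an assumption. One million simulated sets of z-statistics gave:

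| Tests | Assumed outcome correlation | Family-wise error |
|---|---|---|
| 2 (fatigue only) | not needed | about 9.1% |
| 6 | 0 | 24.8% |
| 6 | 0.3 | 23.8% |
| 6 | 0.5 | 21.9% |
| 6 | 0.7 | 19.2% |
| 6 | 0.9 | 14.9% |

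**4. Power for CIS-fatigue at 24 per group if α were split.** The standard error is 9.3 × √(2 × 0.8425/24) = 2.464, so 8/2.464 = 3.247.

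- α = 0.05: Φ(3.247 − 1.960) = 90.1%.
- α = 0.025 (two arms): Φ(3.247 − 2.241) = 84.3%.
- α = 0.05/6 = 0.00833 (three outcomes, two arms): 72.8%. Restoring 90% needs 35 per group; 35/0.9 rounds up to 39, and 39 × 3 = 117 in total. This uses CIS-fatigue inputs only.

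**The case against.** The best reply is that the text governs. The Outcomes section, the economic evaluation and the sample size all treat fatigue as the primary outcome, and a table heading is the outlier. An aim that names three domains is not a success rule. This stands as an argument about which reading was probably meant, and it is why the fix follows the text. It does not remove the conflict, because Table 3 is the table that the Outcomes section cites for its measures and its headings are a deliberate classification.

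A reader might also infer that the trial can claim primary success on any of six or more tests. The documents do not support that. No passage states such a rule, and the research questions join the domains with *and*. If all three had to be positive, false-positive error would not inflate; power would fall instead. Counting each SIP-68 domain or each visit as a further primary test would likewise assume a scoring and testing scheme that the article does not state and that an analysis plan may settle.

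The absence of an adjustment for two active arms is not an error here either. Exercise and CBT are posed as separate questions, and whether distinct treatments sharing a control need adjustment is a matter of judgement.

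Finally, it is tempting to say that the formula powers the mean of the three post-treatment visits. It does not: it uses four measurements including entry. With three, the factor is (1 + 2 × 0.79)/3 = 0.86 and n = 28.40 × 0.86 = 24.4, or 25 per group.

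**Conclusion.** The inconsistency is real and should be corrected: one primary outcome in the text and in the sample size, three in Table 3. That the 90% power does not extend to the SIP-68 or SF-36 follows directly from the document and needs no assumption. The sample-size arithmetic itself is correct.

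The 15% to 25% error range, against about 9%, is conditional on three things: that Table 3 governs, that any one positive result would count, and that outcome correlations lie between 0.9 and 0. It shows what the ambiguity could cost, not the trial's actual error rate.

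**What to change.** In Table 3, keep only CIS-fatigue under the primary heading and move the SIP-68 and SF-36 rows to secondary. Add one sentence to Outcomes or Statistical Analyses: the efficacy conclusion for each intervention rests on CIS-fatigue compared with usual care, and the SIP-68 and SF-36 results are supportive.

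The change needs no extra patients and leaves the 24 per group and 81 in total as they are. The downside is that activity performance and HRQoL lose primary status, although the stated aims give them prominence. If the sponsor wants to keep three primaries, the protocol needs a stated decision rule and a sample size that matches it, with inputs for the SIP-68 and SF-36.

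A Holm step across the two arms is optional. If used, power at its stricter 2.5% step is about 84% on the stated formula with 24 per group.
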